**Fig. 1 Fig1:**
[figure not shown]
Flow diagram for the unlinked National Joint Registry (NJR) elbow replacement dataset

**Fig. 2 Fig2:**
[figure not shown]
Flow diagram for the linked National Joint Registry (NJR) and NHS England Hospital Episode Statistics-Admitted Patient Care (HES-APC)

### Variables

Most of the data from the NJR and HES-APC can be extracted directly but some of the variables used in this study will be derived using the available data and the methods of how this will be performed are highlighted in this section.

#### Patient related variables

Patient related variables will be extracted from the NJR and HES-APC data. The list of the patient related variables and their data source is displayed in Table 1. Age will be derived from date of birth; socioeconomic status will be derived from postcode as an Index of Multiple Deprivation quintile (2015 version) [23]; and co-morbidities will be derived from the ICD-10 (international classification of diseases, 10th revision) codes reported by HES-APC. The list of co-morbidities for each patient will include all co-morbidities available in the HES-APC hospital episodes up to and including the primary TER. The co-morbidity list will be used to calculate the original Charlson Comorbidity Index [24] and a revised version of Charlson Index using an updated weights which are calibrated using English data due to differences in coding practice and hospital patient population characteristics [25]. If BMI is not reported, then the value will be derived from the height and weight variables if they are reported. The indication for surgery in will be reported as five categories: acute trauma, inflammatory, trauma sequalae, osteoarthritis and other. Procedures that are reported as Essex Lopresti on the NJR will be included in the acute trauma category if the injury is acute or in the trauma sequelae if the injury is chronic. The decision whether the Essex Lopresti injury is chronic or acute will be decided by the admission type and duration of surgery wait on the HES-APC data. Non-elective admissions and elective admissions with less than two weeks from decision for surgery to the date of surgery will be considered as acute injuries. Procedures reported as avascular necrosis will be added to the “other” category. Multiple indications for surgery can be selected on the MDS forms. In this study the likely primary indication will be selected based on a hierarchy agreed by the research team. Acute trauma will be the primary diagnosis if it is selected followed by trauma sequelae, inflammatory arthritis, osteoarthritis, and then “other” category. Ethnicity was categorised into six categories based on the Office of National Statistics (ONS) Ethnic group classification 6a [26]. If ethnicity is missing from the hospital episode admission for TER surgery, ethnicity will be established from other hospital episodes admissions for that patient where available.

**Table 1 Tab1:** Patient related variables to be included in the planned study

Variable	Dataset	How will data be presented	Method of measurement
Age	NJR	Continuous and age categories	Derived from the date of birth and date of surgery
Sex	NJR	Categorical: Male/Female/Indeterminate	Documented directly using a specified list on MDS collection form
BMI	NJR	Continuous and categorical: Underweight/Normal/Overweight/Obese/Morbidly obese	Documented directly or derived from the weight and height of the patient
Dominant hand	NJR	Categorical: Yes/No/Unknown	Documented directly using a specified list on MDS collection form
ASA	NJR	Categorical: ASA1-ASA5	Documented directly using a specified list on MDS collection form
Indication for surgery	NJR	Categorical: (1) Trauma/Elective (2) Acute trauma/inflammatory/Trauma Sequalae/Osteoarthritis/Other	Documented directly using a specified list on MDS collection form
Socioeconomic status	NJR	Categorical: Indices of multiple deprivation quintiles (2015 version)	Derived from the postcodes and reported as index of deprivation quintiles
Ethnicity	HES	Categorical: Asian, Asian British, or Asian Welsh/Black, Black British, Black Welsh, Caribbean or African/White/Mixed or Multiple ethnic groups/Other ethnic group/Does not apply (students and schoolchildren living away during term-time)	Documented in patient medical records. Classification is based on the ONS group classification 6a [26]
Co-morbidities	HES	(1) Categorical: Acute MI/CHF/PVD/Cerebrovascular Disease/Dementia/COPD/Rheumatoid Disease/Peptic Ulcer/Mild liver disease/Diabetes/Diabetes + Complications/Hemiplegia or Paraplegia/Renal disease/Cancer/Moderate/Severe liver disease/Metastatic Cancer/AIDS/Depression/Anxiety/Osteoporosis (2) Original Charlson Comorbidity Index Hospital (3) Charlson Comorbidity Index Hospital with revised weights	Documented in patient medical records and extracted by admin team at the time of discharge and reported using ICD-10 codes The Charlson Comorbidity Index will be derived from pre-existing condition recorded on HES-APC data using ICD-10 codes

*ASA* American Society of Anaesthesiologists, *BMI*: Body Mass Index, *MI* myocardial infarction, *CHF* congestive heart failure, *PVD* peripheral vascular disease, *COPD* chronic obstructive pulmonary disease

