### Participants

All patients aged 18–100 years old with a primary TER on the NJR elbow dataset from the start of data collection on the 1st of April 2012 to the 31st of December 2022 will be included. Patients are excluded if they did not consent for their data to be used for research purposes, if it is impossible to trace them after surgery, if their ID numbers are invalid, or if the surgery was not performed in England. Several steps will be undertaken to confirm that the included cases are primary TER procedures. This will include (1) ensuring all operative patterns are consistent (2) confirming all reported procedures on the NJR matches the implant components submitted. Unconfirmed procedures and procedures with inconsistent operative patterns (i.e. a sequence of operations where the primary operation is not the first operation in the sequence or where there are multiple primary operations recorded for the same joint) will be excluded from the analyses. The data preparation process and exclusion of non-eligible procedures is summarised in Fig. 1. Eligible NJR procedures will then be linked to the available HES-APC data which includes all patients’ hospital episodes from 23rd of October 1996 to 31st of March 2022. Hospital episodes with invalid ID numbers, implausible dates, unknown discharges dates, and duplicate episodes will be excluded (Fig. 2).

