### Statistical analyses

Descriptive analysis will be performed for all included variables. Frequencies and proportion will be used to summarize categorical variables. The distribution of continuous variables will be assessed using histograms. It is likely that some of the continuous data, such as surgeons’ and hospitals’ volume, will be skewed, therefore, continuous variables will be reported using the median and interquartile range (IQR). The analyses will include summary of all the included population, stratified analysis for elective and acute trauma population, and analysis for each year from 2012 to 2022. The number of procedures performed by surgeons and hospitals will be summarised for the whole population and for each region in England and the results will also be reported on annual basis.

TER rates for different sexes, age categories, socioeconomic status categories and different ethnic groups will be reported. The rates of primary TER per 100,000 persons will be calculated by dividing the number of procedures in the NJR elbow dataset by the corresponding mid-year population estimates published by the Office for National Statistic (ONS). Sensitivity analysis will be performed using the census estimate from 2021. The population estimates by ethnic group reported by ONS will be used to estimate the rates of TER between different ethnicity groups. Age and sex standardised TER rates for each IMD group will be reported. Statistical analyses will be performed using Stata version 18 (StataCorp LP, USA).

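### Comorbidity is taken from all HES-APC history since October 1996, so the searchable look-back grows by ten years across the study and the yearly comorbidity and Charlson summaries can rise as an artefact

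*Protocol article*

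**What the plan says.** The rule is fixed in the protocol article under Patient related variables: "The list of co-morbidities for each patient will include all co-morbidities available in the HES-APC hospital episodes up to and including the primary TER". The same paragraph gives its use: "The co-morbidity list will be used to calculate the original Charlson Comorbidity Index", together with a version that uses weights revised on English data. The article sets no look-back length.

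Under Participants, the linked data cover "hospital episodes from 23rd of October 1996 to 31st of March 2022", after removal of episodes with invalid identifiers, implausible dates, unknown discharge dates or duplication. Eligible replacements run "from the start of data collection on the 1st of April 2012 to the 31st of December 2022 will be included".

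Under Statistical analyses, all included variables are to be described, and the results are to include an "analysis for each year from 2012 to 2022".

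Table 1 says two things about the codes. On their origin: "Documented in patient medical records and extracted by admin team at the time of discharge". On the index: "The Charlson Comorbidity Index will be derived from pre-existing condition recorded on HES-APC data using ICD-10 codes".

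**The concern.** An ever-recorded variable can only stay the same or increase when more history is searched. With a fixed calendar start and no window, each later year of surgery gets about one more year of search. A rising yearly series of comorbidity prevalence or Charlson score could then reflect sicker patients, longer records or both, and the planned tables could not tell these apart. This matters because the Introduction names the kind of patient who receives the operation as the first focus of the study.

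A second, smaller question concerns the index episode. It contains the operation and is coded at discharge. An acute event after surgery that is coded in that episode, such as an acute myocardial infarction, meets the inclusion rule for the baseline list. Table 1's reference to pre-existing conditions points the other way, and the article does not say how the two are to be reconciled.

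**Working it through.** The article states no look-back length, so there is no planned figure to reproduce. The check uses its own dates.

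**Inputs**
- Start of HES-APC data: 23 October 1996 (Participants).
- End of HES-APC data: 31 March 2022 (Participants).
- First eligible operation: 1 April 2012 (Participants).
- Last eligible operation: 31 December 2022 (Participants). HES-APC ends nine months earlier, so 31 March 2022 is the last operation date with hospital data.

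**Available look-back** = (operation date − 23 October 1996) in days / 365.25
- Operation on 1 April 2012: 5,639 / 365.25 = 15.44 years.
- Operation on 31 March 2022: 9,290 / 365.25 = 25.43 years.
- Growth: 25.43 − 15.44 = 9.99, which is 10.0 years from unrounded values. Ratio: 25.43 / 15.44 = 1.65.

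At the midpoint of each reporting period, look-back is 15.8 years for April to December 2012, 16.7 for 2013, 20.7 for 2017, 24.7 for 2021 and 25.3 for January to March 2022.

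**What this could do to prevalence (illustration on an assumption).** Suppose a condition is first recorded at a constant rate r per year. The share ever recorded over look-back t is 1 − exp(−r × t). The document gives no value of r, so a range is shown.

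| Assumed r per year | t = 15.44 years | t = 25.43 years | Difference (percentage points) |
|---|---|---|---|
| 0.25% | 3.8% | 6.2% | 2.4 |
| 0.5% | 7.4% | 11.9% | 4.5 |
| 1% | 14.3% | 22.5% | 8.2 |
| 2% | 26.6% | 39.9% | 13.3 |
| 3% | 37.1% | 53.4% | 16.3 |

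With a common window W, the share is 1 − exp(−r × W) in every year, so the artefact is zero. At r = 1% and W = 15.44 years it is 14.3% throughout. The table shows direction and is an upper illustration. It treats everyone as unrecorded in 1996 and equally likely to be recorded in every year since, whereas recording concentrates in later life.

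**Index episode (no arithmetic).** Three statements, side by side:
1. The linkage rule (Source of data) requires the operation date to lie between the start and end of the matched episode, so that episode can contain postoperative time.
2. The inclusion rule keeps that episode, and Table 1 places coding at discharge.
3. Table 1 bases the Charlson Index on pre-existing conditions, but the article gives no rule that separates these from new events within the episode. The categorical list, which includes acute myocardial infarction and cerebrovascular disease, does not carry that qualifier.

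An acute postoperative code can therefore enter the list. How many patients this affects cannot be derived.

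**The case against.** The strongest reply on look-back is that using all history maximises capture, and that the drift may be small. Chronic conditions such as diabetes or COPD may be coded again at later admissions, including the index episode that the plan deliberately keeps. For these, years beyond the first fifteen may add little. This stands as a limit on size: the tabulated shifts are not estimates. It does not remove the unequal search, which follows from the stated rule and dates.

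It can also be said that comorbidity is purely descriptive here, with no comorbidity-adjusted model. That is correct and limits the importance of the point.

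On the index episode, Table 1 already restricts the Charlson Index to pre-existing conditions, and an article may leave code lists to a fuller document. That also stands in part, and it is why the point is one of reconciling two statements.

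A reader might infer three stronger things that the document does not support:
- **That postoperative events are counted as baseline disease.** The text shows only that they can be. Table 1 points the other way for the Charlson Index, and an event coded in a later episode of the same stay falls after the cut-off.
- **That an event during the stay counts as comorbidity in place of a serious adverse event.** The Outcome section defines serious adverse events as complications that cause an admission. That wording alone leaves out non-fatal events during the stay, whatever the comorbidity rule says. Nothing makes the two lists mutually exclusive.
- **That a cohort after reconfiguration would look sicker still.** That depends on the look-back a future study adopts. The Discussion proposes comparing future practice with this study's outcomes and specifies no case-mix comparison.

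**Conclusion.** The main point holds. Available look-back rises from 15.4 to 25.4 years, a factor of 1.65, and this rests only on dates and a rule stated in the article. The yearly comorbidity and Charlson summaries can therefore rise as an artefact. How far they would rise is unknown, because any prevalence figure depends on a recording rate that the document does not give.

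The secondary point holds as an unreconciled pair of statements: the inclusion rule admits the index episode, while Table 1 speaks of pre-existing conditions.

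The effect is confined to descriptive comorbidity results. The number and rate of replacements are untouched. The point merits correction before analysis but does not threaten the main objective.

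**What to change.** **Look-back.** For the yearly comorbidity and Charlson summaries, apply one common look-back to every patient, counted back from the operation. It should be no longer than the 15.4 years available to the earliest patient. The exact length is for the study team to choose and justify, since the article supports no particular shorter window. Keep all-available history as a sensitivity analysis. The work is a date filter; the cost is that some remote diagnoses are no longer counted in the main yearly series.

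**Index episode.** Reconcile the text under Patient related variables with Table 1. Take codes for acute events (acute myocardial infarction, acute stroke) only from episodes before the index admission. Chronic conditions, including chronic cerebrovascular disease, may still come from the index episode, so that long-standing disease first coded at the replacement is not lost. The work is a split of the code list. The cost is that an acute event that occurred before surgery but was coded only in the index episode would be missed.

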#### Implant related variables

Implant related variables will be derived from the NJR data only. They are based on classifying each implant in the NJR data. In this study, the classification used for the NJR annual report will be used [27]. There are different combinations of the Latitude implant reported by the NJR 20th annual report. In this study Latitude will be classified as Latitude Legacy, Latitude EV, or Latitude mix (i.e., EV and Legacy components). The list of the implant related variables and how they will be measured is shown in Table 2.

**Table 2 Tab2:** Implant related variables to be included in the planned study

Variable	Dataset	How will data be presented	Method of measurement
Fixation type	NJR	Categorical: Cemented/Uncemented	Derived from implant codes on the MDS form
Implant classification	NJR	Categorical: Linked/Unlinked	Derived from implant codes on the MDS form and the list of components (e.g. if a linkage component was submitted with a likable implant)
Implant type	NJR	Categorical: Coonrad-Morrey/Discovery/Latitude (Legacy, EV, Mix)/GSB III/MUTARS/Nexel/IBP	Derived from implant codes on the MDS form
If RHR was used	NJR	Categorical: Yes/No	Derived from implant codes on the MDS form and the list of components

*NJR* National Joint Registry, *RHR* radial head replacement

#### Surgeon and hospital related factors

Most of the surgeon and hospital variables used in this study are not directly reported but will be derived from the available data (Table 3). The NJR includes pseudonymised codes to represent the surgeon who performed the surgery and the hospital where the surgery was performed. This data can be used to calculate the surgeon’s and hospital’s volume. In this project, the annual number of TERs will include all TERs from the 1st of January to the 31st of January of that year. The year 2012 will be excluded from this analysis because data is only available from April 2012.

**Table 3 Tab3:** Surgeon and hospital related variables to be included in the planned study

Variable	Dataset	How will data be presented	Method of measurement
Funding	NJR	Categorical: NHS/Independent sector	Documented directly using a specified list on MDS collection form
Grade of primary surgeon	NJR	Categorical: Consultant/Other	Documented directly using a specified list on MDS collection form
Surgeon volume	NJR	Number of TERs performed by a surgeon per year by surgeons	Derived from pseudonymised codes representing the surgeon in charge of patient care. It represents the number of TERs performed from 1st of January to the 31st of December of each year
Hospital volume	NJR	Number of TERs performed by a hospital per year by surgeons	Derived from pseudonymised codes representing the hospital where TER was performed It represents the number of TERs performed from 1st of January to the 31st of December of each year
Regional volume	NJR	Number of TERs per year by surgeons by region	Derived from the hospital where TER was performed. It represents the number of TERs performed from 1st of January to the 31st of December of each year
Duration of elective wait	HES	Number of days waiting	Derived from the date which it was decided to admit the patient and actual admission date
Post-operative duration of stay	HES	Number of inpatient days following surgery	Derived from the date of surgery and date of discharge
Elective admission type	HES	Categorical: General admission/Day case admission	Documented in patient medical records

The duration of elective wait and the length of post-operative stay will be derived from the HES-APC data. To establish the duration of elective wait, the difference in days between the date on which it was decided to admit the patient and the date of surgery will be calculated. The length of post-operative stay will be derived from the difference in days between the date of the TER and discharge date. Elective admissions will be classified into general admissions or day case admissions. Day case admission will be derived from the admission method and spell duration variables on HES-APC. For an elective procedure to be classified as day case it must be an elective admission and has a spell duration of 0 days.

### Outcome

The primary outcome in this proposed study will be the number and/or the rate of provision of primary TER. Secondary outcomes will include the duration of elective wait and post-operative duration of stay measured in days. Current trends will be described by reporting the outcomes on annual basis.

Serious adverse events (SAE) within 30 days and 90 days from the index TER will also be reported. SAE will be defined as any severe medical complications leading to hospital admission, including pulmonary embolism, myocardial infarction, lower respiratory tract infection, acute kidney injury, urinary tract infection, cerebrovascular events, and all-cause death. SAE will be extracted from the HES-APC data and identified using ICD-10 codes.

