**Methods:**

This analysis will use the National Joint Registry (NJR) elbow dataset and link it with NHS England Hospital Episode Statistics-Admitted Patient Care (HES-APC). It will include eligible patients from the start of the NJR elbow dataset in April 2012 to December 2022. The main objective is to determine the incidence of TER in England. Age-sex standardised rates will be calculated for groups including different ethnicities, and socioeconomic backgrounds, using the mid-year population data provided by the Office for National Statistics. This planned analysis will summarise patient characteristics such as age, sex, body mass index (BMI), hand dominance, American Society of Anaesthesiologists (ASA) grade, indication for TER, socioeconomic status, and patient co-morbidities. It will also examine implant fixation type, classification, brand/type, and changes over time in implant types used in England. Additionally, it will explore the characteristics and volume of the surgeons and hospitals providing primary TER services, including the grade of the primary surgeons, funding source for surgery, and admission type. The analysis will cover the number of procedures performed by surgeons and hospitals annually in England and in each region of England. Finally, the planned analysis will summarise the elective wait time, postoperative length of stay, and any serious adverse events or re-admissions within 30 and 90 days after the TER.

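### The primary outcome is left open between a number and a rate, and age-sex standardisation is not stated for the annual England series used to describe trends

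*Protocol article*

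**What the plan says.** The abstract (Methods) states the aim: "The main objective is to determine the incidence of TER in England". The Outcome section then defines the primary outcome: "The primary outcome in this proposed study will be the number and/or the rate of provision of primary TER". It adds: "Current trends will be described by reporting the outcomes on annual basis".

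Statistical analyses defines the rate per 100,000 persons as "dividing the number of procedures in the NJR elbow dataset by the corresponding mid-year population estimates" from the ONS, with the 2021 census estimate as a sensitivity analysis. It goes on: "TER rates for different sexes, age categories, socioeconomic status categories and different ethnic groups will be reported". Standardisation appears there once: "Age and sex standardised TER rates for each IMD group will be reported". The abstract extends age-sex standardisation to groups that include ethnic as well as socioeconomic ones. Neither place mentions calendar year or the overall England rate in connection with standardisation.

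The Discussion says that the effect of the service reconfiguration can be monitored by comparing later practice with the results of this study.

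**The concern.** Two things are at issue. First, the wording of the primary outcome allows a count alone, a rate alone, or both, and these answer different questions. A count measures service volume. Incidence, the stated main objective, needs a population at risk.

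Second, the rate as defined has no adjustment for age and sex, and the standardisation that is planned is tied to subgroup comparisons. If the population ages while surgeons treat patients of a given age and sex exactly as before, an unstandardised annual rate still moves. The same applies when a later period is set against this baseline: part of any difference would come from the population and not from the reconfigured service, and that part can grow as the gap between the periods widens.

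**Working it through.** The plan states no trend estimate, sample size or test, so there is no figure to reproduce. The check asks how far each candidate measure would drift if age-specific provision did not change at all.

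**Inputs from the documents.** The rate is procedures divided by mid-year population (Statistical analyses). The illustration runs from 2013 to 2022, nine annual steps, because 2012 covers only April to December. Annual counts ranged from 258 to 463 (Introduction; England and Wales together).

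**Assumed inputs, none given in the documents.** Population growth g of 0.5–0.8% a year. Share aged 65 and over rising from s0 = 17% to s1 = 18.5–19%. TER rate at 65 and over R = 4–8 times the rate below 65. Sex mix unchanged.

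**Growth (affects the count only).** (1 + g)^9 − 1:
- g = 0.005: 4.6%
- g = 0.008: 7.4%

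**Ageing (affects the count and the unstandardised rate).** [1 + s1(R − 1)] / [1 + s0(R − 1)] − 1:
- s1 = 0.185, R = 4: 1.555/1.510 − 1 = 3.0%
- s1 = 0.19, R = 8: 2.33/2.19 − 1 = 6.4%

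**Count, both together.**
- Low: 1.046 × 1.030 − 1 = 7.7%
- High: 1.074 × 1.064 − 1 = 14.3%

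| Measure | Drift with unchanged provision |
|---|---|
| Annual number | about 8–14% |
| Unstandardised rate | about 3–6% |
| Directly standardised rate | 0%, by construction |

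**Wider assumptions.** With total growth of 3–10%, the older share rising from 17% to 18–20%, and a rate ratio of 3–10, the count drifts by 4.5–21.7% and the unstandardised rate by 1.5–10.7%.

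**Scale against random error.** The Poisson 95% half-width of one year's count is 1.96/√n:
- n = 258: 12.2%
- n = 463: 9.1%

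For a log-linear trend over ten years at about 360 procedures a year (near the midpoint of 258 and 463), the sum of squares of the year index is 82.5. The standard error of the slope is 1/√(360 × 82.5) = 0.0058, and the half-width over nine steps is 1.96 × 9 × 0.0058 ≈ 0.10, or about 10%. England alone has fewer procedures than England and Wales, so its random error is somewhat larger. The highest and lowest annual counts differ by a factor of 463/258 = 1.79.

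**The case against.** A reader might infer that the plan commits to an unadjusted annual trend, and that ten years of population growth and ageing would therefore be read as a change in provision. The documents do not support that.

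- **Growth is already handled in the rate.** The mid-year denominator removes it. The 8–14% drift applies only to a raw count presented by itself, which would not meet the incidence objective.
- **No passage says that the annual rate will be unstandardised.** This is inferred from the rate formula and from where standardisation is mentioned. The abstract's list of groups is open-ended, and a fuller plan may cover the annual series.
- **The study is descriptive.** It plans no trend test and does not say that change over time will be attributed to practice. Age-specific and sex-specific rates are planned and would show an age effect if given by year, though that is not stated.
- **Counts and crude rates are legitimate.** The motivation is low volume per surgeon and unit, for which counts are the natural measure.
- **Selective emphasis is a weak worry.** The number is the numerator of the rate, and in the illustration both move in the same direction.
- **The drift is modest.** At 3–6% the rate drift lies below one year's random error, and a later analyst could standardise both periods.

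All of this stands as a limit on the point. It does not settle which measure is primary, nor does it connect the planned standardisation to the series that serves as the baseline. Demographic drift is also systematic, so it does not average out over years as random error does.

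**Conclusion.** The point holds in a limited form. The primary outcome is not fixed, and one permitted reading, a number alone, does not meet the incidence objective. Age-sex standardisation is stated for subgroups and not for the annual England series. Changes in age and sex structure therefore remain in the rate as defined and could be mistaken for changes in provision.

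Under the assumed demographics this amounts to about 3–6% for the rate over 2013–2022, and 1.5–10.7% under wider assumptions. These figures rest wholly on inputs from outside the documents and illustrate the size of the effect; they do not estimate it for England. The documents do not support saying that the trend would be misread, or that growth distorts the planned rate. This is a low-cost improvement to a descriptive plan, not an error that invalidates it.

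**What to change.** In the Outcome section, replace the open choice with the annual rate of primary TER per 100,000 in England as the primary outcome, with the annual number always reported alongside.

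In Statistical analyses, state that the annual England rate will be reported both crude and directly standardised for age and sex to one fixed, named standard population. Add that the standardised series will be used when changes in the rate over time, or against later years, are interpreted as changes in provision. Counts and crude rates stay in the report as descriptions of service volume; the standardised rate need not replace them for that purpose.

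The cost is about one sentence in each section. Procedure counts by age and sex and ONS denominators are already needed for the planned age, sex and IMD rates, so no new data are required.
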